### Ethical Considerations

This study has obtained ethical approval from Carleton University Research Ethics Board-B, ethics clearance ID: 119784, ensuring strict adherence to participant confidentiality, anonymity, informed consent procedures, and data protection, in compliance with applicable institutional and ethical guidelines. No identifiable data will be included in any part of the research. Participants will be given the opportunity to enter a drawing for gift cards valued at US $25 each, specifically for completing the surveys.

## Results

Data collection took place in October and November 2023; the anticipated results are scheduled for publication in 2024. We anticipate several key findings. First, randomization is expected to have groups with closely matched demographic characteristics, ensuring a balanced starting point for our analysis. Second, we anticipate that usability will be significantly higher for the ChatGPT intervention than for conventional methods, reflecting the potential benefits of AI-assisted learning. In addition, regarding ChatGPT’s use in assignments, we expect to observe students expressing concerns about data privacy and plagiarism, consistent with prior literature findings on these issues. The potential correlation between usability and learning outcomes is a significant aspect to consider in our study. Understanding how usability impacts learning outcomes not only is critical for this study but also lays the foundation for future investigations. By quantifying the effect sizes of both the learning and usability effects in this study, we can better inform the calculation of sample sizes for larger RCTs on this topic. These data will be invaluable for designing robust experiments and ensuring that our research can provide meaningful insights into the relationship between usability and educational outcomes.

Furthermore, it is our anticipation that despite these concerns, learning outcomes will remain consistent across both interventions. We expect to observe that while these concerns may be raised, the overall effectiveness and educational benefits of ChatGPT are not compromised. Our study seeks to determine whether these anticipated results are confirmed. These data will contribute to a better understanding of the potential impacts of integrating AI into health sciences education.

This study is expected to contribute to the identification of key areas and challenges concerning the use of AI as an educational tool, specifically examining its benefits and challenges for students. By doing so, it aims to facilitate the establishment of comparable frameworks for future academic endeavors. In addition, the findings will enlighten educators about the potential advantages and barriers associated with integrating AI into educational activities for university students.

We expect this study’s findings to be disseminated through multiple channels. The study will undergo a rigorous peer review process for publication in a reputable, peer-reviewed journal. Subsequently, the results will be initially shared with the community in the health sciences department, ensuring timely access for the scientific community. Furthermore, we intend to submit the results of this study to relevant national conferences to provide a platform for knowledge exchange and engagement with a broader audience.

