### Study Hypotheses

The study’s hypotheses are as follows:

*Null hypothesis:* there is no significant difference in technology usability and learning outcomes between students who use ChatGPT (group A) and those who use conventional web-based tools (group B) for accessing resources and completing assignments.*Alternative hypothesis:* there is a significant difference in technology usability between students who use ChatGPT (group A) and those who use conventional web-based tools (group B) for accessing resources and completing assignments.*Exploratory hypothesis:* the learning outcomes of students who use ChatGPT (group A) will significantly differ from those of students who use conventional web-based tools (group B) for completing their assignments. This hypothesis proposes that the choice of intervention (ChatGPT or conventional web-based tools) may influence the learning outcomes and explore the interaction between usability and learning outcomes.

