### Data Analysis

This study aims to compare the 2 interventions in terms of usability, student perception, and learning outcomes. The crossover design allows for within-group and between-group comparisons, enabling a comprehensive analysis of students’ perceptions of the use of the intervention and its impact on their learning, as well as the effects of the intervention on their learning outcomes.

The use of an identification code will anonymize data. The data set will be exported from the datasheet and imported into the SPSS software (version 28.0; IBM Corp) for Mac, where the data will be subjected to analysis with a confidence level of 95%. Descriptive statistics, including the calculation of frequencies, will be performed on the sociodemographic variables of the students. The usability scale and grades at each assessment time will be summarized using mean and SD. The nonparametric Wilcoxon test will be used to compare the differences between these variables.

The frequencies, means, and SDs of each item of the SUS scale will be calculated and compared using the McNemar or chi-square and Wilcoxon tests, respectively. In addition, the usability scores and the grades of each group will be correlated using Spearman correlation.

For the analysis of perception and usability outcomes, we will use the Spearman correlation coefficient to assess the relationship between the 2 scales. This statistical approach was chosen to measure the strength and direction of the associations between variables when the data may not conform to a linear pattern. Using the Spearman correlation coefficient, we aim to better understand how perceptions and usability factors are interrelated, providing a robust basis for our research findings and conclusions. To assess the internal consistency of the scales, Cronbach α coefficient will be calculated for both constructs and for each individual item.

To categorize the students into groups of low and high performance (using a cut-off value of 80) and classify the SUS scale into high and low usability groups (with a cut-off value of 50), appropriate statistical tests will be applied. Specifically, Fisher exact test or Pearson chi-square test will investigate the associations between the categorized scales and sociodemographic characteristics.

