## Discussion

### Overview

This study will compare the use of ChatGPT and web-based conventional tools in terms of usability, student perception, and learning outcomes. ChatGPT is expected to be perceived as more usable than conventional tools. However, we anticipate that both groups will achieve similar learning outcomes. Furthermore, our findings may align with those of previous studies that underscore the significance of AI in education, albeit with concerns related to data privacy, as students increasingly recognize the importance of AI in their learning experiences.

This study is expected to provide details on students’ perceptions of using AI to perform their learning assignments. The results of this study will be compared with those of the literature. In recent years, there has been a growing body of research on AI, focusing on its applications in various fields, including medical education, health care, radiography, and ophthalmology [5,33,34]. Many of these studies use cross-sectional and qualitative research methods to explore the perspectives and attitudes of professionals and students [33,35,36]. Despite variations in the specific field of study, some common themes emerge from this research. These themes include a generally positive attitude toward AI’s potential benefits, a widespread lack of formal AI education among participants, concerns about data privacy and ethical implications, and a clear and urgent need for structured AI education to be integrated into relevant curricula [33,35]. These studies collectively underscore the importance of preparing individuals in these fields for the increasing role of AI in their respective domains.

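### The article expects similar grades and asks whether that is confirmed, but its grade analysis can only detect a difference and its exploratory hypothesis predicts one

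*Protocol article*

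**What the plan says.** In the protocol article, the Results section, written before any results, lists expected findings. One is that "learning outcomes will remain consistent across both interventions". The next sentence expects that, although students may raise concerns, "the overall effectiveness and educational benefits of ChatGPT are not compromised". The section then states: "Our study seeks to determine whether these anticipated results are confirmed". The Overview under Discussion repeats the point: "we anticipate that both groups will achieve similar learning outcomes".

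Study Hypotheses points the other way. The null covers both usability and learning outcomes and is one of no difference. The exploratory hypothesis is that "the learning outcomes of students who use ChatGPT (group A) will significantly differ" from those of students using conventional tools.

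For the analysis, the learning-outcomes row of Table 1 gives only mean and SD, on a 0-100 scale. Data Analysis says "The usability scale and grades at each assessment time will be summarized using mean and SD", followed by "The nonparametric Wilcoxon test will be used to compare the differences between these variables". Grades also enter Spearman correlations with usability, and a split at 80 that is examined against sociodemographic characteristics. Neither of these compares the two interventions. No equivalence or non-inferiority hypothesis, margin or interval criterion is attached to the grade expectation.

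**The concern.** There are two problems.

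First, the conclusion in view does not match the tool. A Wilcoxon test is built to reject equality. When it does not reject, the data may fit no difference, but they may also fit a difference that an educator would care about. If the study is to say whether similar grades were confirmed, something beyond the p value has to carry that statement.

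Second, the article holds two opposite expectations for the same outcome. The exploratory hypothesis predicts a significant difference, while Results and Discussion predict none. A reader cannot tell which finding would count as support.

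At stake is the message on grades. A real but modest fall with ChatGPT could fail to reach significance and then be summarised in the reassuring terms that the article already uses.

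**Working it through.** **1. Does the planned sample size bear on grades?** The Sample Size section gives 84% against 50%, 90% power, 95% confidence, and the Fleiss method with continuity correction, for 45 students.

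- Mean proportion: (0.84 + 0.50)/2 = 0.67.
- Uncorrected n per group: [1.96 × √(2 × 0.67 × 0.33) + 1.2816 × √(0.84 × 0.16 + 0.50 × 0.50)]² / 0.34² = 38.1.
- Corrected n per group: (38.1/4) × [1 + √(1 + 4/(38.1 × 0.34))]² = 43.8, rounded up to 44.

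The stated 45 is reproduced to within one, as a per-group figure for two independent proportions. Adding 10% gives 50. No grade, SD or margin enters, so the number says nothing about how precisely grades will be compared.

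**2. What could a non-significant grade result hide?** Inputs:

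- n = 45 pairs, the figure before the allowance for loss.
- Two-sided 5% test. The article gives 95% confidence; two-sided is assumed.
- SD of within-student grade differences: not in the article. Assumed to be 10 points, range 8 to 15.
- Paired t-test arithmetic as an approximation to the planned Wilcoxon test.

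Formulas: SE = SD/√45. The 95% interval half-width is 2.015 × SE, where 2.015 is the 97.5th percentile of t on 44 degrees of freedom. The chance of a non-significant result is the probability that a noncentral t on 44 degrees of freedom, with noncentrality (true difference)/SE, lies between −2.015 and 2.015.

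| Assumed SD | SE | 95% CI half-width | Non-significant, true fall of 3 | Non-significant, true fall of 5 |
|---|---|---|---|---|
| 8 | 1.19 | 2.4 | 31% | 2% |
| 10 | 1.49 | 3.0 | 50% | 9% |
| 15 | 2.24 | 4.5 | 74% | 41% |

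For example, at SD 10 a 3-point fall has noncentrality 3/1.49 = 2.01, almost exactly the critical value, so the test misses it about half the time. Replacing t by the normal distribution moves these figures by at most about two percentage points (48% and 8% at SD 10).

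**3. What would a margin-based conclusion need?** Take an illustrative margin of ±5 points, a true difference of zero, and two one-sided tests at 5% each. Power is approximately 2Φ(5/SE − 1.68) − 1.

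- SD 10: 2Φ(3.35 − 1.68) − 1 = 91%.
- SD 15: 2Φ(2.24 − 1.68) − 1 = 42%.

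With a ±3-point margin at SD 10, the normal version, 2Φ(3/SE − 1.645) − 1, gives 29%. A claim of similarity is therefore attainable at this sample size for some combinations of margin and SD and out of reach for others. The margin is not in the article; it is used here only to show scale.

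**The case against.** A reader might infer that the trial will treat a non-significant grade result as equivalence, or that it is an equivalence trial with the wrong test. The article supports neither reading. It contains no such decision rule, and its objectives contain no equivalence aim. The formal null and the exploratory hypothesis are difference-type and match the Wilcoxon test. The similarity statements are expectations, and the sentence about confirmation also covers usability and student concerns and leaves the answer open.

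Other points count in the plan's favour:

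- The article intends to quantify effect sizes for learning, which tells a reader more than a p value. The stated purpose, however, is to size later trials, not to judge whether grades are similar.
- The sentence saying that benefits are not compromised refers back to students' privacy and plagiarism worries. It is only partly about grades.
- Grades are listed as secondary and the grade hypothesis as exploratory, so not sizing the trial on them is ordinary practice and is no fault in itself.
- The SD and margin above are assumed. At the central SD a 5-point fall is missed only 9% of the time, and nothing in the article establishes that 3 points matters.
- Data collection is reported as finished, so requiring an equivalence margin now is debatable.

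A further defence is that a separate analysis plan may deal with this. That does not remove the point: the article itself fixes the hypotheses and the test, and itself states the similarity expectation that they cannot confirm.

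**Conclusion.** The point stands as a mismatch and a contradiction within the article. Results and Discussion anticipate similar grades and ask whether this is confirmed; the planned grade comparison can only detect a difference; and the exploratory hypothesis predicts one. The plan offers no route by which similarity could be shown.

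The contradiction rests on the text alone. The size of the risk rests on the assumed SD, on 45 complete pairs, and on normal-theory approximations to a Wilcoxon analysis. Under those assumptions, a non-significant test is weak evidence against a 3-point fall throughout the range considered, and weak evidence against a 5-point fall only towards SD 15. Severity is moderate to low, because the outcome is secondary and exploratory.

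**What to change.** 1. Report the within-student grade difference, ChatGPT minus conventional tools, with its 95% confidence interval.
2. Do not describe grades as consistent or similar, or benefits as uncompromised, on the strength of a non-significant test. State that no difference was detected and give the interval.
3. Conclude similarity only if a justified margin on the 0-100 scale was fixed and dated before the grades are unblinded, and the 90% confidence interval (two one-sided tests at 5%) lies wholly within it. If no such margin exists, leave the similarity conclusion out.
4. Reconcile the exploratory hypothesis in Study Hypotheses with the expectations in Results and Discussion, so that grades carry one stated expectation.

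The cost is one interval and some rewording; no new data are needed. The downside is that similarity becomes harder to claim. Even with truly equal grades and a ±5-point margin, it would be shown only about 42% of the time at SD 15.

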## Discussion

### Overview

This study will compare the use of ChatGPT and web-based conventional tools in terms of usability, student perception, and learning outcomes. ChatGPT is expected to be perceived as more usable than conventional tools. However, we anticipate that both groups will achieve similar learning outcomes. Furthermore, our findings may align with those of previous studies that underscore the significance of AI in education, albeit with concerns related to data privacy, as students increasingly recognize the importance of AI in their learning experiences.

This study is expected to provide details on students’ perceptions of using AI to perform their learning assignments. The results of this study will be compared with those of the literature. In recent years, there has been a growing body of research on AI, focusing on its applications in various fields, including medical education, health care, radiography, and ophthalmology [5,33,34]. Many of these studies use cross-sectional and qualitative research methods to explore the perspectives and attitudes of professionals and students [33,35,36]. Despite variations in the specific field of study, some common themes emerge from this research. These themes include a generally positive attitude toward AI’s potential benefits, a widespread lack of formal AI education among participants, concerns about data privacy and ethical implications, and a clear and urgent need for structured AI education to be integrated into relevant curricula [33,35]. These studies collectively underscore the importance of preparing individuals in these fields for the increasing role of AI in their respective domains.

A study focused on assessing medical students’ knowledge, attitudes, and perceptions of AI chatbots in health care revealed that while medical students generally held positive attitudes toward AI, they also had data protection and monitoring concerns. Students expressed a desire for more comprehensive AI education integrated into their medical curriculum, emphasizing the importance of preparing them for AI’s role in health care [35]. A systematic review of the utility of ChatGPT, an AI-based conversational large language model, in health care education, research, and practice highlighted numerous benefits and emphasized the need for a code of ethics and responsible use guidelines for AI chatbots, such as ChatGPT in health care and academia, to maximize their potential while addressing limitations and risks [8]. A Canadian study explored how undergraduate medical students in Canada perceive AI in medical education. The survey conducted with 486 students from all 17 Canadian medical schools revealed that while there was a consensus that AI will be important in future medicine and should be formally taught, many students believed that there are currently insufficient educational opportunities related to AI. Interviews with students echoed these concerns, emphasizing the need for AI integration into the medical curriculum to better prepare future physicians for the changing health care landscape [33].

These studies have provided valuable insights into students’ and professionals’ knowledge, attitudes, and perceptions regarding AI and AI chatbots in health care and related fields. They generally indicate positive attitudes toward AI’s potential benefits, along with concerns about data privacy and the need for structured AI education. However, it is essential to acknowledge that these studies have limitations, including potential biases inherent to their study designs. Therefore, further research is needed to delve deeper into the utility and students’ perceptions of AI chatbots, such as ChatGPT, in health care and academia. To address these gaps and gain a more comprehensive understanding, we plan to conduct a crossover RCT. This proposed study will enable us to systematically investigate the effectiveness and user perceptions of ChatGPT in specific health sciences and educational contexts while controlling for potential biases and limitations observed in previous studies.

### Limitations and Strengths

Although this study possesses several strengths, it anticipates limitations. First, the sample size may restrict the generalizability of the findings to a broader population of health sciences students. However, this constraint is balanced by the advantages of a focused investigation within a specific academic institution, allowing for in-depth exploration. Second, the relatively short intervention period may limit the ability to capture long-term effects or changes in participants’ perceptions over time. Nevertheless, this controlled timeframe allows for a rigorous assessment of immediate impacts. Moreover, although the study specifically examines the use of ChatGPT, acknowledging the limitation of generalizability to other AI tools, it contributes to the existing body of knowledge in this field. Finally, participants’ self-reported data, including their perceptions and experiences, may introduce response bias. However, this method aligns with the quantitative nature of the research and provides rich insights into participants’ perspectives. Despite these anticipated limitations, this study’s strengths lie in its focused investigation, controlled timeframe, and quantitative approach, all of which contribute valuable insights into the usability, perceptions, and potential benefits of using AI in health sciences education.

It is important to note that the next phase of this study, which involves subsequent qualitative data collection and analysis, is strategically designed to address some of these limitations. By investigating participants’ experiences and perceptions through focus groups, the next phase of the study aims to provide a more comprehensive understanding of the long-term effects, nuanced challenges, and potential benefits associated with AI use in health sciences education. This approach complements the quantitative phase of the study presented in this protocol and enhances the overall robustness of the study’s findings, thereby mitigating some of the anticipated limitations.

## Appendix

Multimedia Appendix 1 Tips to interact with artificial intelligence.

Multimedia Appendix 2 Guidelines for equitable use of artificial intelligence.

## Abbreviations

AI: artificial intelligence
CONSORT: Consolidated Standards of Reporting Trials
RA: research assistant
RCT: randomized controlled trial
SUS: System Usability Scale
TA: teaching assistant
